### Sequence generation

Randomization will be conducted using a computer-generated random allocation sequence using SAS 9.4 (SAS Institute Inc., Cary, NC, USA) by a statistician with no clinical involvement in this trial.

### Allocation

The allocation shall proceed via duplicate, sealed, numbered envelopes, which will be stored by the clinical trial quality control inspectors and the principal investigator. The blind bottom shall not be opened without reason during the trial. The outcome assessors and the statisticians will not participate in the treatment; they will perform the outcome evaluation and the statistical analysis independently.

### Randomization and blinding

Enrolled participants will be randomly assigned to TEAS, sham, or control group (1:1:1). An independent, blinded statistician will generate the block randomization scheme. The table will be managed by an independent researcher who is not involved in the recruitment, treatment, or assessment. The participants will be blinded to the type of treatment. Mock TEAS will be provided with the same lamplight as real TEAS, so the participants will not be able to predict the allocated group based on the appearance of the treatment (Fig. 1). The practitioners will be aware of the allocation arm while the subjects, outcome assessors, and statisticians performing the data analysis will be blinded to the treatment allocation. The schedule for the study is shown in Fig. 2.

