**Methods:**

This study is a protocol for a three-armed, single-blinded, placebo-controlled randomized controlled trial. Ninety participants scheduled for inguinal hernia repair will be randomly assigned to the TEAS group (*n* = 30), sham group (*n* = 30), and control group (*n* = 30). The TEAS group will receive treatment using four portable coin-sized electro-stimulators at both local and distal acupuncture points. The sham group will receive sham treatment with mock electrostimulation. The treatment groups will receive mixed frequency stimulation (alternating at 2 and 100 Hz every 3 s) in continuous mode for 30 min at intervals of 2 h for 24 h postoperatively. The control group will receive postoperative pain control using patient-controlled analgesia (PCA) device. The primary outcome is the total morphine dose received in the postoperative period (mg) using PCA 24 h after surgery. The number of PCA demands (i.e., times the button will be pressed) and delivered bolus doses, score on the Visual Analogue Scale, opioid-related side effects, the requirement for supplemental medications, score on the Hospital Anxiety and Depression Scale (HADS), and blood levels of stress hormones cortisol and prolactin.

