Stimulation will be performed using four portable coin-sized electro-stimulators (StimulAid Inc, Poland). A point-detection function in the device will confirm the correct localization of the stimulator. A combination of the LI4 acupuncture point and peri-incisional ashi points will be utilized to augment PCA analgesia in the postoperative period [16–18]. Not only point selection but also the frequency of stimulation and treatment timing play a critical role in determining the outcome of the intervention. Low-frequency (2 Hz) electrostimulation applied at the acupoints exerts antinociceptive effects mainly by enhancing the release of met-enkephalin (M-ENK), β-endorphin (β-EP), and dynorphin [19, 20]. Therefore, the TEAS group will receive mixed frequency stimulation (alternating at 2 and 100 Hz every 3 s) in continuous mode for 30 min at intervals of 2 h [19, 20]. The device will automatically shut off at the end of each 30-min treatment interval. The intensity of the stimulation will be adjusted to each individual to maintain a slight twitching of the regional muscle and achieve De-Qi sensations, such as soreness, distention, and heaviness. In both groups, electro-stimulators will be applied bilaterally to LI4 (He Gu) and ipsilateral to hernia to two ashi points located within a diameter of 5 cm from the incision site (Fig. 3). The sham group will be provided with the same devices as TEAS with the “in use” light flashing in the usual manner; however, the participants will be told that they may not be able to feel the electrical stimulation. The patients in TEAS and sham groups will be told that they are receiving current stimulation. The PCA therapy and TEAS/sham will be discontinued at 24 h.

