The limitation of our trial is that the assessors/medical personnel is not blinded. Due to the limits of the existing technology, we are unable to blind medical personnel. However, in the future, we may be able to utilize identical pre-programmed devices for sham and real group to resolve the blinding issue. Moreover, this trial is a single-center study. As the curative effect of TEAS may be affected by ethnicity and region, it will be essential to perform multicenter and large sample experiments in the future.

We anticipate that the results will determine whether TEAS with intensified stimulation protocol is a safe and effective option for reducing analgesic consumption and postoperative pain. The results of the study may serve as a platform for developing TEAS-based treatment regimens for enhanced recovery after surgery.

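### The blinding statement claims more than the design provides: the protocol contradicts itself on outcome assessors, and participant masking can cover TEAS against sham only

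*Protocol article*

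**What the plan says.** On assessors, the protocol article makes three statements.

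- Allocation: "The outcome assessors and the statisticians will not participate in the treatment".
- Randomization and blinding: practitioners know the arm, "while the subjects, outcome assessors, and statisticians performing the data analysis will be blinded to the treatment allocation".
- Discussion, limitations paragraph: "The limitation of our trial is that the assessors/medical personnel is not blinded". The next sentence gives the reason: "Due to the limits of the existing technology, we are unable to blind medical personnel".

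On participants, Randomization and blinding first names the three arms and then says "The participants will be blinded to the type of treatment", with no arm excepted. The means is given next: "Mock TEAS will be provided with the same lamplight as real TEAS", so that patients cannot tell their group from how the treatment looks.

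On the control arm, the Methods part of the abstract says "The control group will receive postoperative pain control using patient-controlled analgesia (PCA) device". The Background part of the abstract calls this arm a no-treatment group. The Postoperative analgesia section describes stimulators for the TEAS and sham groups only, and only these two groups are told that they receive current.

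On sensation, the same section has TEAS intensity adjusted to each patient until there is slight muscle twitching and De-Qi sensations. Within its description of the sham group it says "the participants will be told that they may not be able to feel the electrical stimulation".

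**The concern.** Blinding is a stated property of the design, and readers will weigh the results by it. Here the statement is contradicted for one group of people and cannot be true for another.

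The outcomes are of the kind that knowledge of allocation can influence. The primary endpoint is the total morphine dose in mg that the patient draws on demand from the PCA device. Pain on the Visual Analogue Scale (VAS) and anxiety and depression on the Hospital Anxiety and Depression Scale (HADS) are the patient's own reports. A patient who knows that no stimulator has been applied may ask for analgesia differently from one who believes that current is flowing.

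The Study objective section sets out to evaluate efficacy against both sham and standard treatment. The comparison with standard treatment is therefore part of the main claim, and what it can support depends on whether patients were masked in it.

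Assessor blinding matters mainly for secondary data that staff elicit or record, such as VAS scores and opioid-related side effects.

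**Working it through.** The point rests on text, so the check sets the statements side by side. The only arithmetic is a count of arms and contrasts.

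**1. Who is said to be blinded, and where this is contradicted**

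| Group | Randomization and blinding | Elsewhere in the article | Result |
|---|---|---|---|
| Practitioners | Not blinded | Discussion: medical personnel not blinded | Consistent |
| Outcome assessors | Blinded | Allocation: kept out of treatment. Discussion: not blinded | Conflict |
| Analysing statisticians | Blinded | Allocation: kept out of treatment | Consistent |
| Participants, TEAS and sham | Blinded | Mock device with the same light | Means given, for appearance only |
| Participants, control | Blinded, since no exception is made | PCA only, no real or mock stimulator | No means given; not possible as described |

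**2. Assessors.** Allocation and Randomization and blinding treat assessors and practitioners as different people. Read with those sections, the Discussion's mention of assessors adds a second group that is not blinded. The Data management section adds some doubt: it has a surgical nurse collect the data, and does not say whether that nurse is one of the blinded assessors or one of the medical personnel who cannot be blinded. The article does not let a reader settle which statement is right.

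**3. Participants.** Inputs: 90 patients, three arms, allocation 1:1:1.

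- Patients in the arm without a stimulator: 90 / 3 = 30, one third of the total.
- Pairwise contrasts among three arms: 3 × 2 / 2 = 3 (TEAS–sham, TEAS–control, sham–control).
- Contrasts that include control: 2 of 3. In both, patients in one arm wear stimulators and patients in the other do not, so the contrast is open-label for the patient.
- Contrasts that the mock device can mask: 1 of 3, TEAS–sham.

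**4. Masking of TEAS against sham.** The article defends this on appearance. It does not address sensation, although TEAS is titrated to a felt response and the sham is a mock. The warning that stimulation may not be felt stands in the sham description. The following sentence, that patients are told they receive current, names both device groups. Both groups therefore share one message; whether the warning was given to both is not stated.

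**5. Size of effect on the results.** The document gives no figure from which a bias could be calculated, so none is given here.

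**The case against.** The strongest reply is that the Discussion sentence is loose wording. The reason that follows it names medical personnel only, and the remedy proposed for future work, identical pre-programmed devices, concerns staff who handle the stimulators. Allocation and Randomization and blinding agree with each other that assessors are separate and masked. This reading is plausible, and a reader who infers that assessor blinding was absent goes further than the document allows. What stands is that the sentence names assessors, so two current statements conflict and one must change.

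A second reply is that the design already deals with expectation. The sham arm exists for that purpose, the control arm is openly called untreated or standard treatment, the trial is labelled single-blinded, and the lack of staff blinding is declared. This is fair as a defence of the three-arm design. It does not rescue a sentence that claims blinding for all participants.

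A third reply concerns inferences that a reader might add, and it is right on each.

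- The primary endpoint is mg of morphine, limited by the lockout and the 4-hour maximum. Button presses are a secondary endpoint.
- A bias in favour of TEAS on every outcome is not shown. Sham versus control does not involve TEAS at all, and if unblinded staff gave control patients more supplemental analgesia, control morphine could fall, which would work against TEAS.
- A different script in each device arm is likely from where the warning stands, but is not certain.
- The document does not say that the twitching is visible, and nothing in it shows that masking between TEAS and sham failed.

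**Conclusion.** The blinding statement is wrong as written, in two respects.

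- **Assessors:** the article says both that they are blinded and that they are not. The document establishes the conflict, not which side is true.
- **Participants:** blinding is claimed for all, but is described only for TEAS against sham. It cannot hold for the control arm, which is 30 of 90 patients and enters two of the three contrasts. This assumes that control patients wear no real or mock stimulator, which is how every relevant section describes them.

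The consequence is one of interpretation. TEAS versus control and sham versus control include whatever effect knowledge of allocation has on demand for morphine and on self-reported scores. TEAS versus sham is the only contrast that can support an effect specific to stimulation, and its masking is argued on appearance but not on sensation. Size and direction of any bias remain unknown. Blinding of the statisticians is contradicted nowhere.

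**What to change.** 1. Make Randomization and blinding and the Discussion agree on who assesses outcomes and whether those people are blinded. State where the surgical nurse who collects the data belongs. If the Discussion is correct, withdraw the claim that assessors are blinded; if it meant treating staff only, remove assessors from that sentence.
2. Limit the participant-blinding claim to TEAS versus sham.
3. State that TEAS versus control and sham versus control are open-label for the patient. A claim of a stimulation-specific effect then rests on TEAS versus sham, and TEAS versus control is interpreted as including expectation effects.
4. Report as a limitation the difference in sensation between the device arms, and the difference in wording to patients if there was one.

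The cost is wording only; no new data are needed. The Trial status section gives 31/12/2020 as the end of recruitment, and PCA and stimulation stop at 24 h, so it is too late to change what patients were told or to add a question asking them to guess their allocation.

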**Fig.1 Fig1:**
[figure not shown]
Flowchart of the trial process. TEAS, transcutaneous electrical acupoint stimulation

**Fig. 2 Fig2:**
[figure not shown]
SPIRIT figure. The figure shows the phases of the trial and data collection time points

### Sample size justification

Power analysis was performed to determine the number of patients per group sufficient to.

detect a decrease of 30% or more in the PCA opioid analgesic requirements during the first 24 h after surgery, based on the results of the previous studies [13–15]. Each group will include 30 participants, a total of 90 participants. The proper size of the sample was calculated using the following formula:$$Sample\;size=\frac{Z_{1-a/2}{^2}p\left(1-p\right)}{d^2}$$

where:*Z*_1_ − _*a*/2_ is the standard normal variate (at 5% type 1 error *p* < 0.05), − 1.96;*p* is the expected prevalence obtained from a pilot study, − 0.26; and *d* is the absolute precision, − 0.05.

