### Endpoints

#### Primary endpoint

Total morphine dose received in the postoperative period (mg) using patient-controlled analgesia (PCA) device.

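### The sample size formula gives 296 on its own inputs, not 30 per group or 90 in total, and it cannot show power to detect a 30% fall in morphine dose

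*Protocol article*

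**What the plan says.** All of the justification stands in the protocol article under Sample size justification. The stated aim is to "detect a decrease of 30% or more in the PCA opioid analgesic requirements during the first 24 h after surgery", with earlier studies cited for that effect. The resulting size is given as "Each group will include 30 participants, a total of 90 participants". The article then says "The proper size of the sample was calculated using the following formula", and prints n = Z²p(1−p)/d² with three inputs:

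- Z "is the standard normal variate (at 5% type 1 error *p* < 0.05), − 1.96"
- p "is the expected prevalence obtained from a pilot study, − 0.26"
- d "is the absolute precision, − 0.05"

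The dashes before the values are separators, not minus signs. The text does not say what p is a prevalence of. It gives no power, mean, SD or dropout allowance.

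Under Primary endpoint, the outcome is "Total morphine dose received in the postoperative period (mg) using patient-controlled analgesia (PCA) device". The Statistical analysis section compares quantitative outcomes between groups by t-test or Mann–Whitney test. Allocation is 1:1:1 to TEAS, sham and control, and the Study objective names both sham and standard treatment as comparators. Trial status records that recruitment was completed on 31/12/2020.

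**The concern.** There are two separate faults. First, the formula, its inputs and its result are all printed, and the result does not follow from the inputs. Second, even if it did, the formula answers a different question: how precisely one proportion can be estimated. It says nothing about the chance of detecting a difference in mean dose between two randomised arms, and the 30% target never enters it.

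This paragraph is the only justification of the trial's size in the article. It is also what a reader would turn to when judging how informative a non-significant result is. If the detectability statement is not backed by the calculation offered for it, the reader cannot tell whether 30 per arm gives good, moderate or poor power for a 30% reduction.

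**Working it through.** **1. The plan's own figure.** Inputs from Sample size justification: Z = 1.96, p = 0.26, d = 0.05.

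n = 1.96² × 0.26 × 0.74 / 0.05² = 3.8416 × 0.1924 / 0.0025 = 295.65, so 296.

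The article states 30 per group and 90 in total. Dividing 296 by three arms gives about 99, which is neither.

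**2. Could a variant give 30 or 90?**

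| Variant | Result |
|---|---|
| One-sided 5% | 208.2, so 209 |
| Two-sided 1% | 510.6, so 511 |
| d needed for n = 30 | 1.96 × √(0.1924/30) = 0.157 |
| d needed for n = 90 | 1.96 × √(0.1924/90) = 0.091 |
| p needed for n = 30 or 90, with d = 0.05 | about 0.02 or 0.062 |
| Finite-population correction | source population of about 33 (for 30) or 129 (for 90); none is mentioned |
| Two proportions, 0.26 v 0.182 (30% relative drop), 80% power | 444 per group |
| Two proportions, 0.26 v 0.56 (30 points), 80% power | 41 per group |

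None reproduces the stated size from the stated inputs.

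**3. What 30 per arm can detect on the actual endpoint.** For a two-sample t-test, power comes from the noncentral t distribution with 2n − 2 = 58 degrees of freedom and noncentrality δ√(n/2), where δ is the difference in SD units.

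- At two-sided 5%, 80% power needs δ = 0.736, about 0.74 SD.
- At 2.5% for each of two comparisons, it needs δ = 0.814, about 0.81 SD.

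**4. Power for a 30% reduction.** The article gives no SD, so the coefficient of variation (CV) in the comparator arm is an assumption. Two cases are shown, both unadjusted at two-sided 5%.

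- Equal SDs: δ = 0.30/CV.
- SD falls with the mean (constant CV): the TEAS arm's SD is 0.7 times the comparator's. The root mean square SD is CV × √((1 + 0.49)/2) = 0.863 × CV, and δ = 0.30/(0.863 × CV).

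| Assumed CV | δ, equal SDs | Power | δ, constant CV | Power |
|---|---|---|---|---|
| 0.4 | 0.750 | 81.5% | 0.869 | 91% |
| 0.5 | 0.600 | 63% | 0.695 | 75% |
| 0.6 | 0.500 | 48% | 0.579 | 60% |
| 0.8 | 0.375 | 30% | 0.434 | 38% |

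The largest CV that still gives 80% power is 0.30/0.736 = 0.41 with equal SDs, or 0.41/0.863, about 0.47, with constant CV. Any dropout would lower these figures.

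**The case against.** The strongest reply is that a wrong formula on the page does not make 30 per arm a wrong number. The article says that a power analysis was done and cites earlier studies for the 30% effect. Those studies, the pilot and any fuller protocol are not to hand. If the CV is about 0.41 or lower (0.47 if the SD falls with the mean), 30 per arm gives at least 80% power for a single unadjusted comparison. This stands. A reader might infer that the trial is underpowered, and the article does not support that either, because it gives no SD.

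A reader might also infer that the trial should have had 296 patients, or 296 per group. That does not follow. The formula does not address this endpoint, so 296 only shows that the printed arithmetic fails. The ratio of 296 to 30 does not measure a shortfall.

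Taking the target effect from the literature and another parameter from a pilot is ordinary practice and no fault in itself. Nor does the article say that a non-significant result would be read as excluding a 30% reduction. The Discussion calls for larger studies.

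None of this repairs the paragraph. The inputs are printed in full and legible, so this is not detail left to another document, and no unseen document can make them give 30 or 90.

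**Conclusion.** The point holds for the calculation shown. On its own inputs it gives 296, which matches neither stated figure. It is a precision formula for one proportion, applied to a continuous dose compared between arms. It therefore does not support the statement that 30 per group can detect a 30% decrease. That conclusion needs no assumption beyond the printed inputs.

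How much power 30 per arm really has is open. The 0.74 SD figure rests on a two-sample t-test, 30 analysed patients per arm, equal SDs and one comparison at two-sided 5%. It becomes 0.81 SD if two comparisons are each tested at 2.5%. Power for a 30% reduction ranges from 30% to 91% across the assumed CVs and the two SD patterns, so the article shows neither adequacy nor inadequacy. The false statement of how the size was derived must be corrected. A charge of underpowering would go beyond the document.

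**What to change.** Correct the Sample size justification paragraph openly:

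1. Withdraw the prevalence formula as the source of 30 per group, and say how 30 was actually chosen.
2. Name the comparison or comparisons that the size is meant to serve (TEAS v sham, TEAS v control, or both) and the significance level for each.
3. State what 30 per arm delivers: 80% power for about 0.74 SD at two-sided 5%, or about 0.81 SD at 2.5% per comparison.
4. Give the mean and SD of the 24-h PCA morphine dose from the pilot or the cited studies, and the power for a 30% reduction at those values. State whether the SD is taken as equal across arms and what attrition is assumed.
5. Because recruitment is complete, label any new calculation as done after the fact, and do not present it as the original rationale.
6. In reporting, judge whether a 30% reduction is excluded from the confidence interval for the difference, not from this paragraph.

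The cost is one rewritten paragraph. No patients are added, and allocation and tests are unchanged. The stated detectability may turn out less favourable than now claimed.

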### Statistical analysis

Quantitative variables will be reported using the mean and SD (M ± SD) for normally distributed data or median (Me), the lower quartile (Q1), and the upper quartile (Q3) and the range (Min–Max) for skewed data. Kolmogorov–Smirnov Normality Test will be used to verify the normality of distributions. Intergroup differences between the average values of the quantitative data will be assessed using the Student’s *t*-test (*t*-test for independents samples by groups) or Mann–Whitney *U* test. Kruskal–Wallis ANOVA will be used for multiple comparisons (post hoc tests). Additionally, a multivariate analysis, ANOVA for factorial designs (Factorial ANOVA), will be performed to analyze the main effects and their interactions (relationships between independent variables). Qualitative variables (nominal) will be represented as (*n*) and proportions (%). Independence of qualitative variables from the patient status will be verified by the chi-square test or Fisher’s exact test. The significance level will be set at 5%. All data will be analyzed using the Statistica v.13.3 (StatSoft).

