#### Secondary endpoints

The number of PCA demands (i.e., times the button will be pressed) and delivered bolus doses after surgery will be assessed. Score on the Visual Analogue Scale prior to the surgery and at 4, 8, 12, 16, and 20 h after surgery will be recorded. The scale of 0 to 10, where 0 represents the complete absence of pain and 10 represents the worst pain intensity. Moreover, opioid-related side effects and the requirements for supplemental medications (e.g., antiemetics, antipruritics, and analgesics) will be recorded during the postoperative observation period.

The Hospital Anxiety and Depression Scale (HADS) will be used to evaluate the depression and anxiety before and at 24 h after surgery. Blood levels of stress hormones cortisol and prolactin will be measured at the same time points.

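### The between-arm tests for HADS, cortisol, prolactin and VAS make no stated use of the preoperative values already collected, which costs precision on secondary endpoints

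*Protocol article*

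**What the plan says.** Under Secondary endpoints, the Protocol article gives a preoperative value for each of these outcomes. For pain it lists "Score on the Visual Analogue Scale prior to the surgery and at 4, 8, 12, 16, and 20 h after surgery". HADS "will be used to evaluate the depression and anxiety before and at 24 h after surgery". For the hormones: "Blood levels of stress hormones cortisol and prolactin will be measured at the same time points".

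Under Statistical analysis: "Intergroup differences between the average values of the quantitative data will be assessed using the" Student t-test, specified as a "test for independents samples by groups) or Mann–Whitney" U test. It continues: "Kruskal–Wallis ANOVA will be used for multiple comparisons (post hoc tests"). A further model is added: "ANOVA for factorial designs (Factorial ANOVA), will be performed to analyze the main effects and their interactions (relationships between independent variables"). The factors of that model are not named, and no preoperative value is listed in it. The section mentions no ANCOVA, change score or repeated-measures model.

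Under Sample size justification: "Each group will include 30 participants, a total of 90 participants". That number is argued from PCA opioid use alone.

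**The concern.** When an outcome is also measured before treatment, part of its spread after treatment reflects stable differences between patients. A two-sample test of the postoperative values leaves that part in the error term. A model with the preoperative value as a covariate removes it, using data the trial collects anyway.

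The named tests are a stated choice of method for the quantitative data as a whole, so this is more than a detail left to another document. At stake is the width of the confidence intervals, and the power, for pain intensity, anxiety, depression and stress hormones. The Study objective section lists all of these as secondary objectives, and the Background says the trial is also meant to examine the link with stress hormones. No sample size argument is given for any of them.

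**Working it through.** **Inputs.** n = 30 per arm (Sample size justification); two-sided 5% level (Statistical analysis). The correlation r between preoperative and postoperative values is not in the document, so it is an assumption and is shown as a range. The plan gives no precision or power figure for these endpoints, so there is none to reproduce.

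**Variance.** Relative to comparing postoperative values (variance factor 1, equal SDs assumed):
- ANCOVA: 1 − r²
- ANCOVA with the small-sample cost of estimating one slope from two arms of 30: (1 − r²)(1 + 1/56)
- Change from baseline: 2(1 − r)
- Equivalent unadjusted size per arm: 30/(1 − r²)

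| r (assumed) | ANCOVA | with small-sample cost | change score | equivalent n per arm |
|---|---|---|---|---|
| 0.1 | 0.99 | 1.008 | 1.8 | 30.3 |
| 0.3 | 0.91 | 0.926 | 1.4 | 33.0 |
| 0.5 | 0.75 | 0.763 | 1.0 | 40.0 |
| 0.7 | 0.51 | 0.519 | 0.6 | 58.8 |

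The reductions are therefore 1%, 9%, 25% and 49%; at r = 0.7 the variance falls to 51% of its unadjusted value. With the small-sample cost, the break-even point is r² = 1/57, or r about 0.13. Below that, adjustment gains nothing.

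**Detectable difference** with 80% power (normal approximation): (1.960 + 0.842) × √(2/30) = 0.72 SD unadjusted. Multiplying by √(1 − r²) gives 0.69 SD at r = 0.3, 0.63 SD at 0.5 and 0.52 SD at 0.7.

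**Power** for an assumed true difference of 0.5 SD: 49% unadjusted, then 53%, 61% and 77% at r = 0.3, 0.5 and 0.7.

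**Chance imbalance.** The baseline difference between two arms has SD √(2/30) = 0.258 SD and exceeds 0.25 SD with probability 0.33. On average it reaches the outcome multiplied by r: at r = 0.5, a 0.25 SD imbalance shifts the outcome difference by 0.5 × 0.25 = 0.125 SD, about half of the 0.258 SD standard error.

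**The case against.** **The article is condensed.** Covariates for secondary endpoints are often left to a fuller document, and the text does not say whether 24-h values or changes are tested. Testing changes would use the baseline, so it cannot be said that the plan certainly discards it. That stands. But the section names its tests, and none of them can take a covariate. Nor would changes close the gap: they are no better than postoperative values for r up to 0.5, and above that still less precise than ANCOVA (0.6 against 0.51 at r = 0.7).

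**The factorial ANOVA may include the baseline.** This cannot be excluded, since its factors are unnamed. As described, though, it concerns main effects and interactions of factors, is additional to the two-sample comparisons, and lists no preoperative value. It does not answer the point.

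**Nothing is invalid.** This stands in full. A reader might infer that chance baseline imbalance biases the results or passes straight through to them. It does not: under randomisation the unadjusted standard error already allows for it, and an imbalance passes through only in proportion to r. A reader might also infer that the main conclusion is weakened. PCA morphine has no preoperative value, so it is unaffected.

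**The gain may be small.** This also stands. No correlation is documented, and a low one is plausible for VAS because the preoperative score is taken before the surgical pain exists. Nor does the document give effect sizes or SDs that would show the hormone or anxiety objectives to be the ones most likely to be missed.

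**Conclusion.** The point holds as a missed gain in precision on secondary endpoints. Preoperative values are collected for HADS, cortisol, prolactin and VAS, and no between-arm method in the Statistical analysis section is stated to use them. The unadjusted analyses remain valid, and the primary comparison is untouched.

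The size rests on an undocumented correlation: practically nothing at r = 0.1, a modest gain at 0.3, the equivalent of ten more patients per arm at 0.5, and close to a doubling at 0.7. The figures assume equal SDs before and after surgery and a linear relation; the power and detectable-difference figures also use a normal approximation. HADS and the two hormones are the core of the point, and VAS is the weaker case. The change is worth making, but the trial's main conclusion does not depend on it.

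**What to change.** For 24-h HADS-anxiety, HADS-depression, cortisol and prolactin, specify ANCOVA with arm and the same variable's preoperative value as covariate. Use a log scale for the hormones if they are skewed. Report adjusted differences (ratios on the log scale) with 95% confidence intervals for TEAS versus sham and TEAS versus control.

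For VAS, specify a repeated-measures model of the five postoperative scores with arm, time, their interaction and preoperative VAS as a covariate, and name the arm contrast to be reported. State whether any baseline term enters the factorial ANOVA, or drop that model for these endpoints.

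The cost is a few sentences of analysis text, with no new patients, visits or assays. Timing needs care: the Trial status section gives the end of recruitment as 31/12/2020, and outcomes run only to 24 h, so data collection is over. The change should be documented and dated before outcome data are analysed by arm. If that is no longer possible, report the adjusted analysis as post hoc beside the stated tests.
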